##### Occupational therapy assessment

2.2.1.3

The occupational therapist carries out this assessment according to a non-standardized protocol, in order to investigate the participant’s sensory-motor functions, and to consider possible vehicle adaptations. His role is mainly to determine the necessary adaptation of the participant’s car and, thanks to the pluriprofessional advice given at the end of the process, to pass on his opinion to the approved doctor. The occupational therapist also administers questionnaires to obtain information on the participant’s driving before brain injury: Driving Habits Questionnaire (DHQ), Driving Behavior Questionnaire (DBQ) and perceived road risk.

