#### Longitudinal study

2.2.2

Six and 12 months after deliberation of the approved doctor’s opinion, the study investigators of the rehabilitation centers will send questionnaires to each participant of the cross-sectional study in order to study the road risk prediction performance of the tools and professional opinions. These questionnaires can also be completed with the help of a third party or a therapist. They will aim to gather information about participants’ driving in the 6 and 12 months since the opinion on fitness to drive was delivered. The elements investigated will concern:- aberrant driving behavior with DBQ validated in French (Guého et al., 2014),- possible changes in driving habits with DHQ, based on the Canadian Jerome Driving Questionnaire (JDQ©), and- road risk (accident rate and perceived risk).

Six months after the approved doctor’s opinion, participants will also be asked to complete a questionnaire (support for resuming driving questionnaire) to assess the relevance of multiprofessional educational support aimed at encouraging them to resume driving or dissuading them from doing so. In order to limit participant drop-outs, if they do not respond within one month, a reminder is sent by their SMR referent, with a one-month response period and this procedure will be repeated a second time if no response is received after this deadline. After these two reminders, the SMR referent may also contact the participant by phone to ensure that the e-mails have been received. If the participant refuses or does not reply, the SMR referent sends a final e-mail to the participant to inform them that they will be excluded from the longitudinal study.

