### Longitudinal study

3.2

Thanks to the longitudinal study, further analyses will enable us to measure the relevance of the multiprofessional evaluation by comparing each assessment with the road risk. Assessments that are significantly correlated with perceived road risk (as well as with self-reported accident rates) can be considered as good predictors of road risk, further supporting their relevance.

The longitudinal study will also shed light on any changes in driving habits adopted by participants since regularization of their driving license. These analyses will quantify the adoption of coping strategies related to npABI sequelae. Complementary analyses would also enable us to study relationships between changes in driving habits and various assessment scores. For example, a high correlation between changes in driving habits and BIDSAM would highlight the link between metacognition and behavioral regulation (adjusting driving to compensate for cognitive sequelae).

Lastly, this longitudinal study will provide some answers to the HAS recommendation that people with npABI be given the best possible support to resume or stop driving. By questioning participants, the support for resuming driving questionnaire will highlight the self-reported relevance of multiprofessional assessment for:- Judging their driving ability- Becoming aware of their driving ability- Obtaining information and advice from the team- Adjusting their driving (in the case of unrestricted fitness to drive)- Understanding the reasons for unfitness to drive or driving restrictions (in the case of fitness with restriction codes)- Dissuading them from driving (in the event of unfitness)

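### Self-reported accident rates are to support the assessments as predictors of road risk, but they are not tied to driving exposure, which depends on those same opinions, and no pre-injury accident item is listed

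*Protocol article*

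**What the plan says.** Section 2.2.2 (Longitudinal study) states that at 6 and 12 months after the approved doctor's opinion "the study investigators of the rehabilitation centers will send questionnaires to each participant of the cross-sectional study". The forms cover driving "in the 6 and 12 months since the opinion on fitness to drive was delivered". They include the driving behavior questionnaire (DBQ), the driving habits questionnaire (DHQ) and "road risk (accident rate and perceived risk").

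On late replies, the same section says "if they do not respond within one month, a reminder is sent by their SMR referent, with a one-month response period". Those still silent get one more reminder on the same terms. A telephone contact may follow, with no time limit given.

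Before follow-up, section 2.2.1.3 (Occupational therapy assessment) lists what is collected about driving before the injury: "Driving Habits Questionnaire (DHQ), Driving Behavior Questionnaire (DBQ) and perceived road risk". Accidents are not in that list.

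Section 2.2.1.7 (Approved doctor visit) allows three results: fit, fit temporarily and/or with restrictions, and unfit. Section 2.2.1.8 (Participant support) describes what may follow. After a favorable opinion there are formalities and possible changes to the vehicle. After an unfavorable or reserved one, the options include restrictions, rehabilitation, waiting for a new assessment, or other means of transport.

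Section 3.2 (Longitudinal study, in the Discussion) gives the planned inference: assessments significantly correlated with perceived road risk ("as well as with self-reported accident rates") may be considered good predictors of road risk.

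**The concern.** An accident reported as a driver needs time at the wheel. Here that time is partly a consequence of the opinions whose predictive value is being judged. The approved doctor takes the multiprofessional evaluation into account, and the result decides whether, when and under what restrictions the person drives. Someone who stops driving after an unfavorable opinion will report no accidents as a driver, however accurate the opinion was. In the correlation described in section 3.2, that person counts against the assessment.

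The stake is the direction of the conclusion. An assessment that correctly identifies unsafe drivers, and so keeps them off the road, can look uninformative or even wrong. An assessment with little influence on driving is affected less. The study is meant to guide which assessments professionals rely on, so this comparison matters even though it is secondary and exploratory.

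A second, smaller issue is the absence of a listed pre-injury accident item. The accident rate is the only follow-up risk item that counts events instead of asking for a judgement, and it is the one with no listed pre-injury value.

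**Working it through.** The article states no figure for accident frequency, exposure time or reply window, so there is none to reproduce. The check is a comparison of sections plus simple arithmetic.

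**1. Who reports accidents, and who drives.**
- Reporting: every participant of the cross-sectional study (section 2.2.2).
- Driving: depends on the approved doctor's result (2.2.1.7) and on what follows it (2.2.1.8).
- Analysis: correlation of each assessment with the self-reported accident rate (3.2). The word rate is used, but the article gives no denominator.

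**2. Effect of unequal exposure.** Let a person's monthly accident rate while driving be r and the months driven T. The expected number of accidents is r × T. For an unfavorable (U) and a favorable (F) opinion:

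ratio of expected counts = (r_U / r_F) × (T_U / T_F)

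The count shows an excess for U only if r_U / r_F is greater than T_F / T_U.

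The article gives no delay between opinion and resumption, so the delay is an assumption. Take recall fixed at 6 months, with F resuming at once (T_F = 6):
- U resumes at once: T_U = 6 and T_F / T_U = 6/6 = 1. There is no distortion.
- U resumes after 3 months: T_U = 6 − 3 = 3 and T_F / T_U = 6/3 = 2. A doubled monthly rate would be hidden completely, since 2 × 3/6 = 1.
- U does not drive: T_U = 0. The expected count is 0 whatever the underlying risk.

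This does not rely on late replies or on an open-ended recall period.

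**3. Pre-injury comparison.**
- Before the injury (2.2.1.3): DHQ, DBQ, perceived road risk.
- At follow-up (2.2.2): DHQ, DBQ, perceived road risk, accident rate.

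Perceived risk at follow-up is asked relative to before the injury (2.3.2.1, Secondary criterion C), so it carries its own comparison. The accident rate does not.

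**4. Reply timing.** Latest reply within the stated periods = nominal month + 1 + 1 + 1:
- month-6 form: 6 + 3 = 9
- month-12 form: 12 + 3 = 15

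Only if respondents report everything up to the day they reply do these delays become exposure: 9/6 = 1.50 (50% more) and 15/12 = 1.25 (25% more). Under the same condition, a late replier who resumed at once has 9 months at the wheel, against 3 for a punctual replier who resumed after 3 months: 9/3 = 3. If the form fixes the period at 6 or 12 months, the excess is 0%.

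**The case against.** The strongest reply is that this is an exploratory study in which the accident rate is neither the main criterion nor the reference outcome of secondary criterion C. Its only stated analytic use is a parenthesis in the Discussion. The article also says rate and not count, and it collects the DHQ at follow-up, with dimensions such as duration and frequency (2.3.2.2, Secondary criterion D). The case report form, which section 2.1 places in a public repository, may define the denominator, the recall dates and further items. All of this lowers the weight of the point. It does not remove it: the article names the inference it will draw and nowhere connects the accident item to the DHQ or to resumption of driving.

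Three stronger readings are tempting and should not be adopted.

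- A reader might infer that the study means to show a rise in accidents over pre-injury driving and cannot. The increase in criterion C belongs to the perceived-risk question, which contains the comparison. The planned correlation with accident rates is between persons and needs no pre-injury value.
- A reader might infer that the 6-month figure covers nine months. The text names 6 and 12 months since the opinion and does not say that recall runs to the reply date. A form about six months still covers six months when returned at month 9.
- A reader might count the overlap of the two periods as an error. Cumulative windows are legitimate, and months 6 to 12 follow by subtraction if both forms are answered consistently.

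Whether the DHQ itself asks about past accidents cannot be checked from the article.

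**Conclusion.** The point holds in a limited form. As described, the correlation between assessments and self-reported accident rates mixes the risk while driving with the amount of driving, and the second depends on the opinions under evaluation. The expected direction is against assessments whose unfavorable opinions keep people off the road. The size cannot be given from the article. With fixed 6-month recall and an assumed 3-month delay in resuming, a two-fold difference in monthly accident rate would be masked; with no driving at all, any difference would be. This rests on exposure differing by opinion, which sections 2.2.1.7 and 2.2.1.8 make likely but do not quantify.

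The missing pre-injury accident item restricts what the accident rate can say and breaks no stated analysis. The 50%, 25% and three-fold figures are conditional on recall running to the reply date, and the three-fold figure also on the assumed delay. They should not be presented as properties of the plan. The change is worth making because it is cheap and improves an inference that the article announces.

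**What to change.** 1. At months 6 and 12, record whether driving was resumed and on what date.
2. Express accidents per month or per km actually driven, using the DHQ already collected. Report people who did not drive as having no exposure, not as having a zero rate. Alternatively, restrict the accident analysis to those who resumed driving, and say so in the conclusion.
3. Add one item on accidents before the injury to the occupational therapy questionnaire.
4. Unless the case report form already does so, anchor the recall period to the month-6 and month-12 dates and record the completion date. If it does, one sentence in the article settles this part.

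The cost is a few date fields, one extra baseline question and some rewording of the two follow-up forms. The pre-injury accident item will carry recall error, as do the other recalled pre-injury items. Restricting to those who resumed driving leaves fewer participants and limits the result to people who were driving.

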### Analysis

2.3

Participant characteristics and assets will be described and compared. Reasons for refusing to participate will be collected. Descriptive statistics on participant characteristics will be presented. The characteristics of participants included will be compared with those of non-included participants in the eligibility register to ensure their representativeness. Quantitative variables will be described in terms of mean, standard deviation, median, interquartile range and extreme values. Qualitative variables will be described in terms of absolute frequency and percentage per modality. The alpha threshold for statistical significance is set at 5%; 95% confidence intervals will be presented. All the variables collected for people included in the study will be described. Missing data will not be replaced in this study and some participants might be secondary excluded from certain analyses. Sub-group analyses may be carried out, if statistically robust, depending on the number of fitted cars required and the conclusion of the medical examination.

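### Silence at month 6 is treated as leaving the longitudinal study, so month-12 data that could be obtained are given up; any opinion-dependent reply then distorts month-12 sensitivity and specificity further

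*Protocol article*

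**What the plan says.** Section 2.2.2 of the protocol article says that the investigators "will send questionnaires to each participant of the cross-sectional study in order to study the road risk prediction performance", at 6 and at 12 months after the approved doctor's opinion.

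The handling of non-reply is set out step by step:

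- First reminder: "if they do not respond within one month, a reminder is sent by their SMR referent, with a one-month response period".
- Second reminder: "this procedure will be repeated a second time if no response is received after this deadline".
- Optional call: "the SMR referent may also contact the participant by phone to ensure that the e-mails have been received".
- End of the ladder: for refusal and silence alike, one last message goes out, and its stated purpose is "to inform them that they will be excluded from the longitudinal study".

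Section 2.3 Analysis adds: "Missing data will not be replaced in this study and some participants might be secondary excluded from certain analyses". The representativeness check stated there concerns entry to the study: "The characteristics of participants included will be compared with those of non-included participants in the eligibility register". Sections 2.3.2.1 and 2.3.3 compute accuracy, sensitivity, specificity, PPV and NPV from the counts of Table 4. The reference in that table is perceived road risk, which is known only from a returned form. Section 2.3.2.2 (criterion D) needs the month-6 and month-12 questionnaires for its difference scores.

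**The concern.** Two features of the rule matter. It applies to the longitudinal study as a whole, although the event that triggers it is a single unanswered form. It also gives the same consequence to a person who declines and to a person who simply did not answer. Someone in the second group has withdrawn nothing and might well answer six months later.

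Two things are at stake at month 12. The first is information: the cohort is planned at no more than 100, and each form lost shrinks the cells of Table 4 and the change scores of criterion D. The second is bias. Unfavorable and reserved opinions lead to restrictions, delay or alternatives to driving (2.2.1.8), and the follow-up forms ask about driving, so reply may plausibly differ by opinion. If it does, sensitivity and specificity computed on responders are distorted (partial verification bias). A rule that requires reply at both visits compounds that difference.

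**Working it through.** **Timing.** One month for the first reply, one after the first reminder and one after the second: 1 + 1 + 1 = 3 months. A month-6 non-reply therefore closes at about month 6 + 3 = month 9, before the month-12 mailing. The article describes no route back.

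**Inputs.** The documents give no reply rate, sensitivity, specificity or prevalence, so there is no figure of the plan to reproduce. From the documents: N = 100 (2.1), the layout of Table 4 and the formulas in 2.3.3. Assumed: true Se = Sp = 0.70; prevalence of increased perceived risk 0.30; reply at each visit 0.90 if favorable and 0.70 if unfavorable; visits independent given the opinion; every non-reply is silence, not refusal.

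**Full data.** RP = 100 × 0.30 × 0.70 = 21; FN = 9; RN = 100 × 0.70 × 0.70 = 49; FP = 21.

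**Month 12.** Multiply the favorable cells (RN, FN) and the unfavorable cells (RP, FP) by the chance of being analysed. Without the rule these are 0.90 and 0.70. With it, both visits must be answered: 0.90 × 0.90 = 0.81 and 0.70 × 0.70 = 0.49.

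| Month 12 | RP | FN | RN | FP | n | Se | Sp | Accuracy |
|---|---|---|---|---|---|---|---|---|
| Everyone replies | 21 | 9 | 49 | 21 | 100 | 0.700 | 0.700 | 0.700 |
| No exclusion rule | 14.7 | 8.1 | 44.1 | 14.7 | 81.6 | 14.7/22.8 = 0.645 | 44.1/58.8 = 0.750 | 0.721 |
| Exclusion rule | 10.29 | 7.29 | 39.69 | 10.29 | 67.56 | 10.29/17.58 = 0.585 | 39.69/49.98 = 0.794 | 0.740 |

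The rule costs 81.6 − 67.56 = about 14 participants. The error in Se is 0.115 with the rule and 0.055 without it; in Sp, 0.094 and 0.050. Dropping the rule removes about half the bias. The rest comes from analysing responders unadjusted.

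**What does not move.** PPV is 14.7/29.4 = 10.29/20.58 = 0.500, and NPV is 44.1/52.2 = 39.69/46.98 = 0.845, as in the full data. When reply depends only on the opinion, each row of Table 4 is scaled as a whole and the row-wise metrics are unchanged.

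**Other assumptions.**

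- Equal reply of 0.80 at each visit: 100 × 0.80 × 0.80 = 64 analysed with the rule, 80 without. No bias either way.
- Reversed direction at a single visit (0.70 favorable, 0.90 unfavorable): Se 0.750, Sp 0.645. The bias changes sign.
- Month-6 non-responders less willing at month 12, replying at 0.40 whatever the opinion: favorable 0.81 + 0.10 × 0.40 = 0.85; unfavorable 0.49 + 0.30 × 0.40 = 0.61. Then n = 58 × 0.85 + 42 × 0.61 = 74.9, Se = 12.81/20.46 = 0.626, Sp = 41.65/54.46 = 0.765. The gain falls to about 7 participants but does not vanish.

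**The case against.** The strongest reply is that the article never says in so many words that the month-12 mailing is cancelled; it says questionnaires go to every cross-sectional participant at both times. That is correct. Loss of month 12 is the plain reading of an exclusion from the longitudinal study that falls at about month 9, not an explicit instruction, and the full protocol on OSF may be clearer. If centers do mail month 12 regardless, the article needs only a clarification.

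The reminders, the optional call and the possibility of completing forms with help should also keep non-reply low. They reduce how often the rule applies, but not what it does when it applies. Opinion-dependent reply is an assumption too. The loss of forms does not depend on it; the bias does. And with so few participants reporting increased risk, a shift of this size lies inside sampling error: a 95% Wilson interval for 12 of 22 runs from about 35% to 73%. That is a fair limit on its visibility, though the rule also shrinks the denominator of sensitivity, from 22.8 to 17.6 in the illustration.

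Three stronger readings are tempting, and the text does not carry them:

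- A reader might attribute all distortion from opinion-dependent reply to this rule. At month 6 the rule contributes nothing, and at month 12 only part.
- A reader might infer that a missed month-12 form deletes a valid month-6 form. Nothing says that received forms are discarded; 2.3 speaks of exclusion from certain analyses and of describing all variables collected.
- A reader might fault the absence of a weighting model. Ruling out replacement of missing values does not rule out weighting, and such detail commonly sits in an analysis plan that is not shown.

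**Conclusion.** The point holds as a narrow one. The article states a rule that ends follow-up for silent participants who have not refused, and its plain reading forfeits their month-12 data for criteria C and D. Under the assumed reply rates of 0.90 and 0.70 this costs about 14 of 100 participants at month 12 and roughly doubles the bias in sensitivity and specificity; with less willing late responders the loss is about 7. With reply unrelated to the opinion, only forms are lost. The true size is unknown because no reply rates are given. PPV and NPV are unaffected if reply depends on the opinion alone. The main concordance criterion, criteria A and B, and criterion E (explored at 6 months only) are untouched by the loss of month 12. The change is worth making before the month-12 mailings, since those data cannot be recovered afterwards.

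**What to change.** Reword the end of the reminder paragraph in 2.2.2 so that:

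- non-reply counts as missing for that visit only;
- the month-12 questionnaires go to everyone who has not refused, including month-6 non-responders;
- refusal alone ends follow-up;
- every form received is kept and analysed at its visit.

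The final e-mail should be changed to match. The cost is one changed instruction to the centers and a few more mailings and reminders.

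Optionally, and as a sensitivity analysis only, report sensitivity and specificity with responders weighted by the inverse of the reply rate within each category of the opinion being evaluated. In the illustration 14.7/0.70 = 21 and 8.1/0.90 = 9 restore Se = 21/30 = 0.70, and the same step restores Sp. This is exact only if reply depends on that opinion alone. A larger model with TRIP and eight centers is not advisable with about 20 non-responders. For the approved doctor's opinion, which participants report themselves (2.2.1.7), the weights can cover only those whose opinion is known.

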### Analysis

2.3

Participant characteristics and assets will be described and compared. Reasons for refusing to participate will be collected. Descriptive statistics on participant characteristics will be presented. The characteristics of participants included will be compared with those of non-included participants in the eligibility register to ensure their representativeness. Quantitative variables will be described in terms of mean, standard deviation, median, interquartile range and extreme values. Qualitative variables will be described in terms of absolute frequency and percentage per modality. The alpha threshold for statistical significance is set at 5%; 95% confidence intervals will be presented. All the variables collected for people included in the study will be described. Missing data will not be replaced in this study and some participants might be secondary excluded from certain analyses. Sub-group analyses may be carried out, if statistically robust, depending on the number of fitted cars required and the conclusion of the medical examination.

